## 5. Expected Results

This study aims to validate and investigate how a computer vision-based approach measuring knee ROM in people who have had TKR surgery can be used in clinical practice. The findings of this research project could lead to improvements in the diagnosis, monitoring, and management of knee stiffness after TKR. Unlike current methods—which require in-person evaluations and subjective assessments [7]—data could be captured over regular time points, providing a comprehensive view of the recovery trajectory.

Understanding the priority of patients and healthcare professionals from focus groups will enable consideration of how the computer vision-based approach can be scaled for use in healthcare settings. Consideration should be given to fitting the approach with regular clinical workflows and integrating it with existing healthcare records [29]. The barriers and facilitators to implementation will be identified—such as training requirements, infrastructure limitations, and user acceptance. Scaling the approach for use in broader healthcare settings will require addressing potential infrastructure challenges—including smartphone access and patient support—and data privacy considerations to protect sensitive videos [30]. The computer vision-based software can analyse videos in real time, meaning the videos do not need to be stored, thus minimising privacy risks and data storage demands.

Once the computer vision-based approach has been validated, adaptive machine learning models could support its implementation into the healthcare system. These models could adjust to the recovery trajectories of patients who underwent TKR and improve the timing of interventions. The establishment of personalised thresholds for interventions by using collected data to automate the system [31] could enable the early identification of pain and stiffness. This development will be guided by the results and insights gained from the focus groups to ensure alignment with user requirements.

The primary focus of this study is on short-term recovery from TKR surgery; however, the computer vision-based approach could also be used for longer-term monitoring. Knee ROM and peak flexion during gait are reduced in people with severe knee osteoarthritis compared to those with moderate or asymptomatic knee osteoarthritis [32]. Furthermore, peak knee flexion during stance progressively reduced between asymptomatic, moderate, and severe osteoarthritis groups [32]. This suggests that monitoring knee ROM—or other kinematic variables—could help identify early signs of osteoarthritis progression. Personalised thresholds could then be used to identify candidates for intervention, such as additional physiotherapy.

### 5.1. Strengths

The computer vision-based application only requires a single camera, such as a camera on a smartphone. Mobile phone literacy levels are high and are well accepted in research by older adults [33]. This accessibility makes the technology promising for widespread use in remote monitoring. As a result, it could lead to improved patient engagement and more frequent monitoring.

The computer vision-based software could help widen accessibility to specialists who may not be local. This could help provide better service access, particularly in more remote areas. This technology can be used alongside face-to-face telemedicine to improve remote patient care. Remote assessments are also valuable for monitoring and tracking changes in physical movements at increments unrealistic for in-person visits in the NHS. This could allow for the earlier identification of problems of stiffness, which would facilitate earlier intervention.

This study will also employ focus groups which can generate rich, qualitative data through interactive discussions. Comparisons made between participant experiences can provide valuable insights which would be lost in individual interviews [34]. Focus group discussions are flexible and allow for further insights into unexpected but relevant ideas to be obtained [35]. This will help provide a detailed understanding of the benefits and challenges of implementation into clinical practice.

### 5.2. Limitations

The computer vision-based approach is designed to assess only physical movements, so it cannot replace the requirement for clinician interaction. The software does not address wound care and symptoms beyond pain and swelling, so in these instances, input from healthcare professionals is required. The software should therefore be considered as an adjunct to current clinical practice rather than a replacement of appointments.

This study employs convenience sampling and purposive sampling methods. While these approaches are justified given the exploratory nature of the research, they may introduce selection bias, limiting the generalisability of the findings. To mitigate this, demographic questions will be asked, ensuring that the results are interpreted with context. Further research should employ more diverse sampling methods and larger sample sizes in randomised controlled trials to establish the utility of the computer vision-based approach in a clinical environment.

Focus groups tend towards consensus and may mask dissenting views [36]. Facilitators will build rapport with individuals before commencing the focus group and encourage group interaction to ensure participants feel comfortable sharing their views. Focus groups also tend to attract more confident individuals, which may result in the population being misinterpreted [37]. Healthcare professionals will be recruited from a wide range of clinical backgrounds to ensure varied opinions. Participants who underwent TKR will have a variety of experiences, which is unlikely to be linked with confidence levels.

### 5.3. Ethics and Dissemination

The protocol was evaluated and approved by the London—Chelsea Research Ethics Committee (IRAS ID 339937, REC reference 24/PR/0438) and will be carried out in accordance with the Declaration of Helsinki [38], the UK Policy Framework for Health and Social Care Research [39], and the general principles of Good Clinical Practice E6 (R2). Participant data will be pseudonymised and stored securely on the University of Exeter server.

Before any study-related procedure, the participant must sign a consent form, which states that they can withdraw at any time, for any reason, without affecting future care or needing to provide a reason. If a participant withdraws, their previously collected data will still be used. If the participant withdraws due to a serious adverse event, their GP or managing clinician will be followed up with as needed. This will be detailed in the Participant Information Sheet and consent form.

The findings will be disseminated through manuscript publications in peer-reviewed journals and conference presentations.

## 6. Conclusions

Computer vision-based markerless motion capture software could represent an accurate, easy-to-use method of measuring knee ROM, which can provide rapid feedback to patients and clinical teams. Our study will determine the reliability, feasibility, and usability of this approach for measuring knee ROM at home in people who have undergone TKR surgery. Focus groups will provide insights into the integration of the computer vision-based approach into clinical practice. The potential validation of the approach offers clinicians a tool to track recovery trajectories and identify issues earlier in the rehabilitation process.

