Functional tasks that reflect daily movements, such as the sit-to-stand task, could be used to monitor knee ROM. These tasks are easier to complete in the home environment than goniometer measurements and represent functional ability. The sit-to-stand test is recommended for monitoring recovery from TKR surgery [10]. Evidence suggests that sagittal plane knee ROM is decreased during the sit-to-stand task after TKR surgery compared to healthy controls [11], indicating that this task may be used to measure ROM in post-operative patients. Therefore, this study will use the sit-to-stand test to measure ROM in a home-based setting.

The computer vision-based approach offers a non-invasive, objective method to monitor knee flexion in patients with knee stiffness, which could inform treatment decisions to improve outcomes. Currently, no tool exists to remotely and accurately detect early post-surgical knee stiffness. This study seeks to develop a cost-effective tool for measuring and quantifying knee stiffness pre- and post-TKR surgery for use across the NHS. This study also aims to determine its reliability, feasibility, and usability for implementation in the home.

The primary objectives of the study are the following:To provide proof of concept for a computer vision-based approach that measures knee ROM for use in the home setting.To validate the computer vision-based approach in people who have undergone TKR by ascertaining the test–retest reliability of algorithm outputs such as knee flexion/extension angles.To investigate the integration of the computer vision-based approach into clinical practice through focus groups and identify key development areas for successful implementation.

The secondary objectives of the study are the following:To explore how pain influences knee ROM in people who undergone TKR.To investigate the relationship between muscle activation and ROM in people who have undergone TKR and in healthy controls.To describe the association between physical activity and ROM in people who have undergone TKR.To identify the potential risk factors, measured using questionnaires, linked with knee stiffness post-TKR surgery.

This study will be split into three stages: (1) focus groups, (2) validation of the computer vision-based approach for measuring knee range of motion in the laboratory, and (3) home testing. These will be outlined and addressed separately within the protocol.

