### 3.3. Home Testing

Participants will use their own mobile phones or tablet devices to record a video of themselves completing the movement tasks. Participants will upload their videos to REDCap [15,16].

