### 4.2. Validation of Computer Vision-Based Approach

Participants will wear an activity monitoring accelerometer for one week before the experimental session at the university. The accelerometer will be removed at the session. Physical activity monitoring can be repeated in the week following the visit if there are any problems with the data.

Motion capture markers and sEMG electrodes will then be applied. A physiotherapist will administer questionnaires.

A static trial will be recorded, followed by a series of gait/functional tasks. Participants will complete a two-minute walk on a treadmill at a self-selected walking speed. A sit-to-stand test will then be completed three times: participants will start in a seated position and stand up, then sit down without the use of their hands.

Participants will then be asked to complete the timed-up-and-go test (TUG) three times. The participant will start by sitting down in a chair and will stand up, walk forward three metres, turn around a cone, and then walk back to the chair before sitting down. Finally, an overground walking task will be completed three times: the participant will be asked to walk five metres, turn around a cone, and walk another five metres.

Knee range of motion will be measured by a trained physiotherapist. The maximum and minimum angles will be measured using a universal goniometer whilst lying on a physiotherapy couch and whilst seated on a chair.

Participants will be offered the chance to rest between procedures for as long as preferred. The Single Ease Question (SEQ) is a concise post-task questionnaire utilising a seven-point rating scale to gauge the perception of the difficulty or ease of a specific task. The SEQ will be completed after every task. Following the completion of testing, all equipment will be removed from the participant.

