### 4.3. Home Testing

Participants will be asked to set up a camera device (mobile phone/tablet) in their homes and record themselves completing the following:The sit-to-stand test;If possible (within the limitations of the participants’ available space and ability to capture the trial), the TUG walk.

The research team will send the participants an email that will allow them to upload their video files to REDCAP. Videos will be analysed using a custom computer vision-based application. Participants will be asked to complete a System Usability Scale questionnaire [27,28]. The participants will be asked to complete this task within a week of the lab visit.

Descriptive and frequency statistics will be reported for the System Usability Scale questionnaire, and missing data will be reported. Knee ROM will be compared to the $MDC_{95}$ to determine compatibility with lab-based measurements.

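### The article says home reliability will be determined, but the home stage describes no repeat occasion from which a home ICC, SEM or MDC95 could be estimated

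*Protocol article*

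**What the plan says.** Two places in the protocol article promise reliability in the home. The Introduction (section 1) says "This study also aims to determine its reliability, feasibility, and usability for implementation in the home". The Conclusions (section 6) say "Our study will determine the reliability, feasibility, and usability of this approach for measuring knee ROM at home".

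The home stage is set out in sections 3.3 and 4.3. Section 3.3 says "Participants will use their own mobile phones or tablet devices to record a video of themselves completing the movement tasks". Section 4.3 names the sit-to-stand test, and the timed-up-and-go only "within the limitations of the participants’ available space and ability to capture the trial". On timing it says "The participants will be asked to complete this task within a week of the lab visit". Neither section gives a number of recordings or a second home occasion.

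The home analyses in section 4.3 are descriptive System Usability Scale results, a report of missing data, and a comparison of knee ROM with the MDC95 "to determine compatibility with lab-based measurements".

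The reliability methods (mixed model, ICC, SEM, MDC95) are in the data analysis part of section 4.2, which covers the laboratory validation. For that session the article says "A sit-to-stand test will then be completed three times".

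**The concern.** Reliability is the agreement between repeated readings taken under the same conditions on an unchanged knee. To estimate it for self-filmed home readings, at least some participants must be filmed at home on more than one occasion. The described home stage has no such repeat.

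The lab estimate cannot stand in for it. In the lab, the research team positions the equipment. At home, participants place their own device, and position, framing and lighting may change each time. Section 3.2.3 films from several angles to look for an angle effect, so the article itself treats camera angle as a possible source of error.

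The use foreseen in sections 5 and 5.1 is serial remote monitoring. The figure needed for that is how far two home readings differ when the knee has not changed. If the report claims home reliability on the basis of the lab MDC95, users may apply a change threshold that was never estimated for home readings.

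**Working it through.** **The plan's own figures.** The article gives no figure for home reliability. Its only computed figures are the powers in Table 1. They reproduce with a two-sided two-sample t-test at 30 per group (for example, 0.478 against the stated 0.48 at effect size 0.5), but they concern group differences and do not bear on this point.

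**Model.** For one participant, with a single lab value l and a single home value h:

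- l = p + lab error
- h = p + b + s + home error

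Here p is the participant's true ROM, b a home–lab bias common to everyone, and s a participant-specific home–lab difference.

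**What one home occasion identifies.**

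- Mean(h − l) = b, so a common bias is visible.
- Var(h − l) = home error variance + Var(s) + lab error variance.

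The lab term can be estimated from lab repeats. Subtracting it leaves home error variance + Var(s) as one sum. The sum is an upper bound on home error variance; its two parts cannot be told apart.

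**Illustration (assumed values, not from the article).** Lab SEM = 1, participant SD = 5, Var(h − l) = 5. The sum is then 5 − 1 = 4, so home SEM is at most 2. The total home variance about its mean is 25 + 4 = 29 in every row. Home ICC = 1 − home error variance / 29. Home MDC95 = 1.96 × √2 × SEM = 2.772 × SEM, the formula in section 4.2.

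| Home SEM | SD of s | Var(h − l) | Home ICC | Home MDC95 |
|---|---|---|---|---|
| 1.00 | 1.73 | 1 + 3 + 1 = 5 | 1 − 1/29 = 0.97 | 2.77 |
| 1.73 | 1.00 | 3 + 1 + 1 = 5 | 1 − 3/29 = 0.90 | 4.80 |
| 2.00 | 0 | 4 + 0 + 1 = 5 | 1 − 4/29 = 0.86 | 5.54 |

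The variances and covariance of h and l are the same in all three rows, so more participants would not distinguish them.

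**What the MDC95 comparison does tell.** Take b = 0, s = 0, lab SEM = 1 and a lab MDC95 of 2.772. The share of home–lab differences within the MDC95 is 2Φ(2.772 / √(r² + 1)) − 1, where r = home SEM / lab SEM.

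- r = 1: 95.0%
- r = 1.5: 87.6%
- r = 2: 78.5%
- r = 3: 61.9%

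The comparison therefore responds to a noisy home route. Because s or b would lower the share in the same way, it does not estimate home error.

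**Precision if a second home occasion is added.** With n pairs, the home SEM has n degrees of freedom for between-occasion error (n − 1 if a mean shift between the two occasions is removed). The 95% limits are the estimate multiplied by √(n/χ²).

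- n = 30 TKR participants: 0.80 to 1.34
- n = 20: 0.77 to 1.44, assuming that the 40 with complete data in section 2.2.2 split evenly between groups

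These factors describe only the proposed change. They do not measure a loss under the present plan.

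**The case against.** **The number of home recordings is not stated.** Section 3.3 has participants "record a video of themselves completing the movement tasks", which reads as one video, but both home sections also refer to uploads in the plural, and the full protocol may give a count. This stands: a reader might infer that exactly one recording is planned, and the article does not establish that. Several sit-to-stands in one video would still share one set-up on one occasion, and the timed-up-and-go is a different, optional task. Neither supplies a repeat occasion.

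**Noise and bias can be told apart.** A reader might also infer that a noisy and a biased home route would look alike in the data. The design does not support that. A common bias appears in the mean difference and noise in the spread. Only home error and participant-specific differences are confounded.

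**The home comparison is informative.** It uses another day, another device and the participant's own set-up, so it is relevant, though indirect, evidence. This stands, as the shares above show. The multi-angle lab filming also informs on camera position, but not on how much set-up varies between home occasions.

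**The formal objectives do not promise home reliability.** The home objective is proof of concept, and the test–retest objective names no setting. The Introduction sentence could mean general reliability with home use as the goal. The Conclusions sentence is hard to read that way.

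**It is an exploratory pilot, and an analysis plan may add detail.** Pilot status is a fair reason not to enlarge the study, but it then calls for a narrower claim. An analysis plan cannot create repeat occasions that were not collected.

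**Conclusion.** The statement about home reliability goes further than the described home stage can deliver. As described, the study can report lab reliability, the mean home–lab difference, the spread of home–lab differences and an upper bound on home error. It cannot report a home ICC, SEM or MDC95.

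The article contains no data that would put a size on this in degrees. In the illustration, the same data fit home MDC95 values of 2.77 and 5.54, a factor of two. The spread depends on the assumed variances; the lack of identifiability does not.

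The conclusion rests on reading sections 3.3 and 4.3 as describing no repeat home occasion. If the full protocol schedules one and analyses it, the point reduces to saying so in the article.

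**What to change.** Preferred: ask each participant for two home sit-to-stand recordings on different days within the one-week window already allowed, with the camera set up afresh each time and the files uploaded by the existing REDCap route. Add to section 4.3 that home ICC, SEM and MDC95 will be reported for the TKR group from these pairs, together with the mean home–lab difference. State the number of sit-to-stands per recording.

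Cost: a few minutes and one more upload per participant, a minor amendment, and some incomplete pairs. No extra staff or equipment is needed. A participant who returns one video still contributes to the home–lab comparison.

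Otherwise: reword the Introduction aim and the Conclusions so that they claim lab reliability and home–lab agreement of a single home occasion, with feasibility and usability at home. This costs an edit and leaves home repeatability to a later study.

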## Figures and Tables

**Table 1 sensors-24-07334-t001:** Power to detect effect sizes at significance level of α = 0.05.

Effect size	0.2	0.3	0.4	0.5	0.6	0.7	0.8	0.9	1.0
Power	0.12	0.21	0.33	0.48	0.63	0.76	0.86	0.93	0.97

## Data Availability

Not applicable.
